
#### Effects of Training on Spatial Working Memory

##### Overview

To investigate whether training transfers to improvements in spatial working memory, the participants perform a computerized Corsi blocks task. Recent meta-analytic studies conducted with trainees from childhood to older adults [60] and with older adults [61] found negligible effects of video game training on executive functions. The absence of improvement after training may depend on the specific kind of video games used. Studies that used first-person shooter action games reported benefits after training [103,104]. This type of game requires great perceptual abilities, preparedness for unpredictability, and strong emphasis on peripheral visual processing [105]. However, older adults do not like this type of game [55]. Previous findings from our lab yielded mixed results. One study [49] showed no transfer to working memory tasks, while a second study [52] showed that the trainees’ performance improved significantly after training in 2 visuospatial working memory tasks, the Corsi blocks and the jigsaw puzzle. Our results contrast with those of Nouchi et al [88] who found improvements in executive functions after training for 5 weeks. The ineffectiveness of training in spite of the fact that several of the nonaction video games mimic working memory tasks is in line with the findings of Boot and colleagues [54]. Due to these mixed results, the aim of this RCT is to find out whether training effects transfer to the spatial working memory of older adults.

##### Corsi Blocks

The original task [106] consists of a set of 9 identical blocks (3 x 3 x 3 cm) irregularly positioned on a wooden board (23 x 28 cm). The participant is required to point to the blocks in their presentation order. The length of the block sequences increases until recall is no longer correct. Numerous variations have been employed. Here, we use a computerized version with 4 difficulty levels (2, 3, 4, and 5 cubes) with 10 trials per level. The task consists of reproducing the pattern of cubes just presented on the computer screen by writing down the order in which the cubes appeared on a response sheet. The score is derived from the number of sequences reproduced correctly divided by the total number of sequences in the corresponding level (correct/total sequences).

##### Assessing Working Memory Updating

Transfer to working memory after training is assessed with the *n*-back task [107]. We use a computerized version of the task to assess memory updating. In this task, participants indicate whether each visual stimulus in a list matches a stimulus that occurred 1, 2, or 3 stimuli back by pressing a response key with their right hand (counterbalancing index and middle fingers to respond “yes” and “no”).

In sum, the primary outcome measures of this RCT are better performance at posttest than at pretest on a series of tasks: (1) Stroop-negative priming task, (b) oddball task, (3) *n*-back task, and (4) Corsi blocks.

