### Objectives and Hypotheses

The study has 3 main complementary objectives:

1. To examine the behavioral and electrophysiological effects of training older adults with nonaction video games on a series of cognitive tasks designed to assess attentional functions (mainly response inhibition, distraction, and alertness) and to maintain and update verbal and visuospatial working memory. We are also interested in investigating the sustainability of the transfer effects after a 6-month no-contact period.

2. To explore whether motivation, engagement, or expectations account for possible training-related improvements.

3. To examine whether inflammatory mechanisms assessed with noninvasive measurement of CRP in saliva impair cognitive training-induced effects. Inflammatory parameters in the participants obtained by noninvasive saliva-testing methods will be analyzed in biochemical assays to study their possible correlations with cognitive abilities.

We hypothesize that participants in the Lumosity group will improve selective attention assessed with oddball and Stroop tasks and working memory assessed with Corsi blocks and *n*-back tasks in comparison with participants in the active control group. From an electrophysiological perspective, we also hypothetize that in the oddball task the cognitive video game–trained group will improve both the ability to return attention to the relevant task after having been distracted by the novel stimulus (reorientation negativity [RON]) and the ability of the brain to pay attention to the novel stimulus (P300).

Intervention studies conducted with older adults have focused mostly on training a given cognitive function and then measuring the improvement in that function [69,29] and less often on possible changes in neural activity after training [70,71]. Based on the idea that the older human brain still has some plasticity (the ability to change in response to external stimulation), our main hypothesis is that training older adults with appropriate, adapted, and motivating nonaction video games will transfer to cognitive functions that decline with age, such as attention and working memory, by improving these pillars of cognition, which are crucial to maintaining independent living and cognitive health in old age.

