
### General Procedure

Participants in the study were randomly assigned to the cognitive nonaction video game training group or the noncognitive game training active control group. The introduction of an active control group is necessary to avoid placebo effects [54]. Based on the results of our meta-analytic study [61], we use training regimes that are not too long to avoid loss of motivation, and simple, nonaction games that appeal more to elders. According to the temporal discount hypothesis [85], future rewards are less valuable than inmediate rewards. In each session, the trainees play 10 nonaction video games from Lumosity, described below.

The main question examined in our study is whether group (experimental group, active control group) interacts with testing session (pretest, posttest, and follow-up) with regard to performance on a series of cognitive tasks. At least 2 measures for each cognitive domain are acquired to examine transfer of training to untrained tasks demanding attention and working memory. We selected these cognitive domains because these functions deteriorate with aging and tax functions that are critical for independent living. To explore the underlying neural mechanisms of successful transfer of training gains to attentional mechanisms (alert, distraction, and inhibitory effects) and executive control (spatial working memory), electrophysiological data (ERPs) are recorded at pretraining (T1), posttraining (T2), and 6-month follow-up (T3).

All the methodological designs of the primary outcome measures have been constructed using the rules of counterbalancing and stimulus rotation. Response keys are counterbalanced across conditions. The computerized tasks have been programmed using E-Prime 2.0 (Psychology Software Tools Inc). All the statistical analyses of the behavioral results will be performed using SPSS (IBM Corp) and results will be considered significant at *P*<.05, with Bonferroni-corrected post hoc tests performed as appropriate. Continuous EEG activity are recorded in our laboratory with thin electrodes from 34 scalp sites using a NuAmps amplifier as mentioned before.

After randomization and initial assessment (baseline), participants were invited to attend the University Center of Escuelas Pias in Madrid to perform the training sessions in small groups. Trained and active control groups followed 16 training sessions carried out on different hours and days that lasted approximately 10 to 12 weeks.

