Previous studies indicate that deviance distraction occurs because deviant sounds violate the cognitive system’s expectations [89]. Attention capture has been studied from an electrophysiological perspective; the distractor is characterized by a pattern of 3 brain responses [90,91]: (1) mismatch negativity (MMN) and enhanced N1 when the distractor deviates considerably from the repetitive background, (2) P3a (novelty P3), and (3) RON. The MMN response reflects the preattentive detection of an unexpected change in the auditory context and results from the comparison between a memory trace for past acoustic stimuli and the current auditory signal [92]. The P3a response represents the involuntary orientation of attention toward the novel sound [93] and results from an attentional interruption involving frontal areas [94]. RON is also observed when participants are performing a primary task and must redirect their attention toward that task [95]. In this RCT, we undertake electrophysiological recordings to explore the underlying neural mechanisms of successful transfer of training to attentional performance in the oddball task. We expect that the cognitive video game–trained group will improve both the ability to return attention to the relevant task after having been distracted by the novel stimulus (RON) and the ability of the brain to pay attention to the novel stimulus (P300). In our lab, we previously investigated the effect of novelty in young adults using a haptic oddball paradigm consisting of processing textured surfaces [96]. We do not expect this pattern of results in the active control group and thus predict a group × session interaction.

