##### Stroop and Negative Priming Task

Cognitive processes that involve top-down control mechanisms decline with aging but more automatic processes do not [20,22]. The Stroop interference effect reflects the extra time needed to resolve the conflict generated by the irrelevant word meaning in the incongruent condition. One view is that suppression processes relying on executive control are engaged in preventing the irrelevant dimension from taking control of the response [97]. In this study, we investigate the effect of training older adults with nonaction video games on inhibition processing using both behavioral and electrophysiological responses. The task has been designed to assess training-related behavioral and neural changes in Stroop interference and in negative priming (NP). NP (a measure of distractor inhibition) and the standard Stroop effect are assessed in the same task. In the standard NP procedure, participants are presented with pairs of prime and probe displays containing 2 stimuli, the to-be-responded target and the to-be-ignored distractor. In the critical trials, participants must respond to a target that served as a distractor in the previous prime display (the ignored repetition condition). The common finding is that reaction times to targets in the ignored repetition condition are slower than in the control condition, in which the distractor in the prime display is not repeated as the target in the probe display [98-101]. The aim is to investigate whether training older adults improves control, effortful inhibition (Stoop interference), to a greater extent than automatic passive inhibition (NP). The experimental task uses ERPs in combination with the Stroop and NP before and after training to examine the neural correlates of inhibition [102]. Responses for the Stroop analysis will be coded as a function of the congruency between the color and the meaning of the stimulus. Congruent trials are those in which the color of the word coincides with the color in which it is presented. Incongruent trials are those in which the color word does not coincide with the color in which it is displayed. We will also code trials according to the congruency of the previous trial (N−1) in order to compute the NP effect for each trial. The design for the NP effect consists of Group (younger, older adults), Session (pretraining, posttraining, follow-up), and Type of intervention (experimental, active control) as between-participants factors and Repetition (ignored repetition and control) as within-participants factors. Responses for NP analyses will be coded as a function of the relationship between the color of the current target word and the color denoted by the word in the previous trial (distractor). Thus, the ignored repetition trials are those in which the word in the preceding trial denoted the color of the word of the current stimulus. Control trials are those in which both the target (color) and the distractor (word) in the current trial are different from the target and distractor in the previous trial. The ignored repetition condition is always an incongruent trial preceded by an incongruent trial. The aim is to investigate whether the Stroop interference effect in older adults decreases after training while NP does not change. An important addition to the behavioral measures will be the ERP recording while performing the task before and after training to investigate brain activity changes after training.

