### Secondary Outcomes

Improved game performance by the experimental group and the active control group between training session number 1 and 16 (final) is a secondary outcome measure. Efficacy of training will be shown by better performance in the trained video games across the training sessions. Another secondary outcome measure, maintained level of motivation and engagement, will be assessed with a questionnaire administered at training sessions 1, 8, and 16.

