## Results

All analyses will be performed with the SPSS (IBM Corp) program. Statistical significance is considered as a *P* value of <.05. Analyses of variance will be conducted with 2 groups (experimental and active control) at 3 time points (pretest [baseline], posttest [postintervention], and follow-up [after 6 months without contact]). Electrophysiological data will be analyzed using EEGLAB/ERPLAB.

The preparatory phase for using the games has been completed. License to use the games has been granted by Lumosity. Participants have been recruited, pretested, and trained. The final results from this RCT are expected by the end of 2017.

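### The summary of primary outcomes names improvement from pretest to posttest without the active-control comparison that the trial's main question requires

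*Protocol article*

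**What the plan says.** Two kinds of statement about the primary comparison stand in the Protocol article.

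**Before-after wording.** The last sentence under Assessing Working Memory Updating sums up all the primary outcomes: "the primary outcome measures of this RCT are better performance at posttest than at pretest on a series of tasks". The tasks are Stroop-negative priming, oddball, *n*-back and Corsi blocks. The Stroop and Negative Priming Task section frames its aim in the same way: "The aim is to investigate whether the Stroop interference effect in older adults decreases after training while NP does not change".

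**Between-group wording.** General Procedure gives the main question as "whether group (experimental group, active control group) interacts with testing session (pretest, posttest, and follow-up) with regard to performance". Objectives and Hypotheses expects the Lumosity group to improve "in comparison with participants in the active control group". The Oddball Task section says: "We do not expect this pattern of results in the active control group and thus predict a group × session interaction".

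On analysis, the Results section states: "Analyses of variance will be conducted with 2 groups (experimental and active control) at 3 time points". It does not say whether the session effect or the interaction settles the primary outcome.

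Under Secondary Outcomes, improvement on the practised games is described thus: "Efficacy of training will be shown by better performance in the trained video games across the training sessions".

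**The concern.** Participants in both arms take the same tasks at pretest and again at posttest, so some gain from familiarity is plausible in both, whatever they played in between. A criterion that asks only whether posttest beats pretest cannot separate that gain from an effect of the Lumosity games. The Introduction says the active control was added so that improvement could be attributed to the intervention and placebo effects avoided. The summary definition makes no use of it.

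The two statements can give different answers on the same data. If both arms improve equally, the summary sentence is met and the main question is answered in the negative. Because the article does not say which effect of the analysis of variance decides, a reader of the final report could not tell from the protocol which answer was meant to count.

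**Working it through.** The plan gives no figure of its own on this point, so there is none to reproduce. The contradiction follows from the wording; the arithmetic only shows how far the two criteria can diverge.

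**1. Which effect matches which statement**

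| Effect in the 2 × 3 analysis | Question it answers | Statement it matches |
|---|---|---|
| Session | Do scores change over time, both arms together? | Summary of primary outcomes, if read as change in everyone |
| Group | Do the arms differ, averaged over sessions? | None |
| Group × session | Does change differ between the arms? | General Procedure, Objectives and Hypotheses, Oddball Task |

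The summary sentence names no arm. It could mean change in the experimental arm or change in all participants. Neither is a between-group contrast.

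**2. Inputs**

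- From Sample Size: experimental completers at posttest 38 − 8 = 30; control completers 37 − 12 = 25; total 55.
- From General Procedure: significance at .05. Two-sided testing is assumed, as sidedness is not stated.
- Assumed, not in the documents: practice gain *g* = 0.3 SD in both arms, no training effect, and pre-post correlation *r* from 0.5 to 0.8.

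**3. Before-after criterion in the experimental arm**

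SD of change = √(2(1 − *r*)), in units of the task SD. Standardised change *d*z = *g* / √(2(1 − *r*)). Noncentrality = *d*z × √30. The probability is that of a noncentral *t* with 29 df exceeding 2.045.

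| *r* | SD of change | *d*z | Noncentrality | Probability of a significant gain, per task |
|---|---|---|---|---|
| 0.5 | 1.000 | 0.300 | 1.643 | 0.36 |
| 0.6 | 0.894 | 0.335 | 1.837 | 0.43 |
| 0.7 | 0.775 | 0.387 | 2.121 | 0.54 |
| 0.8 | 0.632 | 0.474 | 2.598 | 0.71 |

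**4. Sensitivity**

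- With *g* from 0.2 to 0.5 SD and *r* from 0.5 to 0.7, the range is 0.18 (*g* = 0.2, *r* = 0.5) to 0.93 (*g* = 0.5, *r* = 0.7).
- If the sentence is read as change in all 55 completers, *g* = 0.3 gives 0.59 (*r* = 0.5) to 0.93 (*r* = 0.8).

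**5. Between-group criterion on the same data**

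The pre/post group × session test is a two-sample *t* test on change, 30 against 25. With equal gains its expected difference is 0.3 − 0.3 = 0, so it rejects at its nominal level. Simulation with 40,000 replicates, over gains of 0.2 to 0.5 SD and correlations of 0.5 or 0.7, gave 0.049 to 0.050.

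**The case against.** The best defence is that the summary sentence is a recapitulation, not a decision rule. It names the four tasks and the expected direction, and it gives no test, arm or success criterion. The comparison with control appears in the hypothesis, in the main question and in the oddball prediction, and the stated analysis includes the group factor. No section plans a paired test in one arm. On this view pre-to-post change is just the participant-level measure that the group comparison then uses.

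Much of this stands. The conflict lies in how the outcome is defined; the planned analysis can test the interaction. But the sentence does more than list tasks: it says what the primary outcome measures are, in before-after terms. The Stroop aim repeats that form, and no section says that the interaction decides.

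Two stronger readings are tempting and are not supported.

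- A reader might infer that the trial plans to declare success from change within one arm. The article states no such test, and its stated question points the other way.
- A reader might combine the four tasks and compute the chance that at least one shows a gain. At *r* = 0.5 to 0.8 this would be about 0.83 to 0.99. That needs independent tasks and a rule that any one task suffices, and the article states neither. It would also have to be compared with 1 − 0.95⁴ = 0.185 for the between-group test, not with 0.05.

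The sentence under Secondary Outcomes is a lesser matter. It concerns the trained games, whereas the Abstract puts the primary outcome in transfer. Calling that improvement efficacy is loose wording, not a second instance of the same error.

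**Conclusion.** The point holds as a contradiction within the protocol. The summary of primary outcomes is a before-after statement, the main question is a between-group one, and the planned analysis leaves open which effect decides. A session effect with no interaction would satisfy the first and fail the second.

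The per-task figures of about 0.36 to 0.71 against about 0.05 illustrate what a literal reading would allow. They rest on the assumed 0.3 SD gain and correlations of 0.5 to 0.8, and they describe a paired test that the article does not plan. The contradiction does not depend on them. It should be corrected because it concerns the definition of the primary outcome, and the article reports that posttest assessments were still under way with analysis to follow.

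**What to change.** Replace the closing sentence under Assessing Working Memory Updating with text such as: *For each of the four tasks, the primary outcome is the between-group difference (experimental minus active control) in change from pretest to posttest, tested as the pre/post group by session contrast. Within-group changes are reported descriptively only.* Give the Stroop aim the same comparator, and state in the Results section that this contrast decides the primary outcome.

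The wording should keep to the change contrast. A posttest difference adjusted for pretest (analysis of covariance) is a different estimator and should not be presented as the same thing.

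Optionally, under Secondary Outcomes, describe improvement on the trained games as a check that the games were learned, not as efficacy.

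The cost is a few sentences and no further data. The one downside is a primary criterion that is harder to meet, because a gain shared by both arms no longer counts.

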### Secondary Outcomes

Improved game performance by the experimental group and the active control group between training session number 1 and 16 (final) is a secondary outcome measure. Efficacy of training will be shown by better performance in the trained video games across the training sessions. Another secondary outcome measure, maintained level of motivation and engagement, will be assessed with a questionnaire administered at training sessions 1, 8, and 16.

## Results

All analyses will be performed with the SPSS (IBM Corp) program. Statistical significance is considered as a *P* value of <.05. Analyses of variance will be conducted with 2 groups (experimental and active control) at 3 time points (pretest [baseline], posttest [postintervention], and follow-up [after 6 months without contact]). Electrophysiological data will be analyzed using EEGLAB/ERPLAB.

The preparatory phase for using the games has been completed. License to use the games has been granted by Lumosity. Participants have been recruited, pretested, and trained. The final results from this RCT are expected by the end of 2017.

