### Sample Size

The sample size is based on the number of observations needed to compare the 2 groups of gamers, those trained with Lumosity and those trained with The Sims. As we do not have standard deviations of the scores in our main dependent variables, we used G*Power 3.1 (Department of Psychology) to compute the number of participants, using analysis of variance as a statistical test. For this, using a power of .80, effect size of 0.50, an alpha level of .05, and 2 groups within the *F* test family, we obtained a required total sample size of 57. With a dropout rate of 10%, a total of 63 participants would be required. Rounding up the numbers, we would need more than 64 participants (32×2). As the flow diagram shows, the final number of participants matches these a priori computations closely: 38 participants were assigned to the experimental group (8 lost at posttest) and 37 to the control group (12 lost at posttest).

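### The group x session ANOVA treats pretest as a repeated outcome rather than a covariate: valid under randomisation, but it gives up precision by an amount that depends on a correlation and an effect-size scale the protocol does not state

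*Protocol article*

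**What the plan says.** The Results section of the protocol article fixes the model: "Analyses of variance will be conducted with 2 groups (experimental and active control) at 3 time points (pretest [baseline], posttest [postintervention], and follow-up" after six months without contact. The General Procedure section gives the main question as "whether group (experimental group, active control group) interacts with testing session (pretest, posttest, and follow-up) with regard to performance on a series of cognitive tasks". The section on working memory updating sums up the primary outcomes in the same pre-to-post terms: "the primary outcome measures of this RCT are better performance at posttest than at pretest on a series of tasks", namely Stroop-negative priming, oddball, n-back and Corsi blocks. The article names no covariate and gives no reason for placing pretest among the outcomes.

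The Sample Size section describes a G*Power calculation "using analysis of variance as a statistical test", with these inputs: "using a power of .80, effect size of 0.50, an alpha level of .05, and 2 groups". It does not label the 0.50 as d or f, and it says that standard deviations for the main variables were not available. It reports 38 participants assigned to the experimental group (8 lost at posttest) and 37 to the control group (12 lost).

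**The concern.** Every primary task is measured before training, so each participant's own starting score is available to sharpen the comparison of the two arms. A group x session model uses that score in a fixed way. In the pretest-posttest contrast it subtracts the whole pretest score, which sets the slope of posttest on pretest at 1. If the true slope is below 1, as it is when variances are equal and rho is below 1, the subtraction removes too much and adds noise.

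Two things are at stake. The first is power to detect transfer, in a trial with 55 participants left at posttest. The second is how a chance pretest difference between the arms is handled: in a given data set, the change score over-corrects it, so the arm that happens to start lower looks as if it gained more. The Participants section reports that the arms were similar on demographic and screening-type measures, but does not report balance on the four primary tasks.

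**Working it through.** **Inputs from the Sample Size section.** Posttest completers: 38 - 8 = 30 and 37 - 12 = 25, total 55. Alpha .05; an F test with two groups is non-directional, so two-sided. Effect size 0.50, scale not stated. For two groups d = 2f, so f = 0.50 is d = 1.0.

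**Input not in the documents.** The pretest-posttest correlation rho. It is an assumption here, shown from 0.3 to 0.8.

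**Can the plan's own figure settle d or f?** The section says "we obtained a required total sample size of 57". With the noncentral F distribution (lambda = f² x N, numerator df 1, 80% power), f = 0.50 needs 34 in total and d = 0.50 (f = 0.25) needs 128. Neither gives 57. That figure appears with f = 0.50 and a numerator df of 5, which the section does not state. The stated N therefore does not settle the scale, and both readings are carried below.

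**Variances, taking the SD as 1 at each session.**
- Posttest alone: 1
- Change score: 2(1 - rho)
- Posttest adjusted for pretest: 1 - rho²
- Adjusted over change: (1 - rho²) / [2(1 - rho)] = (1 + rho)/2

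At rho 0.5 these are 1.00, 1.00 and 0.75. The change score is then no more precise than posttest alone, so it forgoes the whole of the 25% reduction that adjustment would give. Below rho 0.5 the change score is less precise than ignoring pretest.

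**Power for the pre-post contrast.** Noncentrality = d / sqrt[variance x (1/30 + 1/25)], with 53 df for the change score and 52 for the adjusted score. Example at d = 0.50, rho 0.5: sqrt(1/30 + 1/25) = 0.271; change score 0.50/0.271 = 1.85, power 44.2%; adjusted 0.50/(0.866 x 0.271) = 2.13, power 55.3%.

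| rho | Variance ratio | d = 0.50: change / adjusted | Gain (points) | f = 0.50 (d = 1.0): change / adjusted | Gain (points) |
|---|---|---|---|---|---|
| 0.3 | 0.65 | 33.5% / 47.6% | 14.1 | 86.5% / 96.7% | 10.2 |
| 0.5 | 0.75 | 44.2% / 55.3% | 11.1 | 95.2% / 98.7% | 3.5 |
| 0.7 | 0.85 | 64.8% / 71.8% | 7.0 | 99.7% / 99.9% | 0.2 |
| 0.8 | 0.90 | 81.8% / 85.5% | 3.8 | 100.0% / 100.0% | 0.0 |

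**The test as planned.** With three sessions the interaction has 2 df, so the change-score equivalence is exact only for its pretest-posttest contrast. Under compound symmetry with rho 0.5, d = 0.50 at posttest and all 55 retained, its power is 45.3% if the effect is fully kept or fully lost at 6 months, and 35.1% if half is kept. Against 55.3% for adjusted posttest, that is about 10 to 20 points lower.

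**Chance imbalance.** The standard error of the pretest difference is 0.271 SD. Given an imbalance of that size, the change-score estimate is shifted by (1 - rho) x 0.271, which at rho 0.5 is about 0.14 SD, over a quarter of a d = 0.50 effect.

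**The case against.** The group x session ANOVA is a legitimate analysis of a randomised trial, answers the question the article poses and matches its pre-to-post definition of the primary outcomes. That stands. A reader might infer that the planned test is biased because it credits regression to the mean as training gain. The documents do not support this: a chance imbalance is equally likely to favour either arm, so the distortion is conditional on the imbalance observed and averages out over randomisations.

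A reader might also take 11 power points as the size of the loss. That figure needs both d = 0.50 and rho = 0.5, and the article states neither. The usual effect size for a G*Power ANOVA is f, and under f = 0.50 the gain is 3.5 points at rho 0.5 and practically nil from 0.7 upwards. This objection also stands. On the other side, the article itself calls video game training moderately effective at best and reports negligible effects on executive functions in meta-analyses, which sits poorly with d = 1.0. Neither reading can be ruled out.

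It may be said that covariates are usually left to the full plan. Here, though, the article does not leave the matter open: it assigns pretest a place in the model.

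Finally, one pretest score per task is too simple. Stroop and negative priming have within-participant conditions, Corsi blocks has four levels and n-back has three. That is fair, and the change has to name the score for each measure.

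**Conclusion.** The point holds as one of efficiency and conditional precision, not of validity. Under equal variances the adjusted comparison has the smaller variance for every rho below 1, by a fraction (1 - rho)/2: 35% at rho 0.3, 25% at 0.5, 15% at 0.7 and 10% at 0.8. With 30 and 25 completers, the gain over the pre-post contrast runs from about 4 to 14 points across that range if 0.50 is d, and from about 0 to 10 if it is f. The planned 2-df interaction does not make up the difference at d = 0.50 and rho 0.5. The size rests on an assumed rho, on an effect-size scale that the article leaves unlabelled, and on equal variances across sessions. Adjustment is worth adopting because it costs almost nothing, even though the gain may be small.

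**What to change.** In the Results section, replace the group x session ANOVA as the test of transfer. For each primary score that will be analysed (each task condition or difference score, and the P300 and RON measures), test the group difference at posttest with the same score at pretest as a continuous covariate. Treat the 6-month score in the same way. Keep pretest out of the outcome vector. Align the main question in General Procedure with this; group x session summaries and plots may stay as description.

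Add one caveat. By the Participants and General Procedure sections, pretest was taken after allocation but before training, so it remains usable as a covariate. Because the design overview says the researchers were not blinded, the plan should state this openly.

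The cost is one degree of freedom per covariate and the work of naming the pretest score that goes with each measure. The pretest scores are already collected, the model is standard in SPSS, and the article places data analysis later in 2017, so the change can be fixed beforehand.
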